### Economic evaluation

The resources used in the delivery of the interventions will be collected at the patient level from records kept by the MDT (Groups A and B), and the care assistants (Group B only). These data will include details of patient contact (number and duration of visits or telephone calls), travel time and distance for home visits, materials, consumables or equipment used, time spent liaising with other professionals (e.g. consultant, GP), and referrals made. Administrative and meeting time of the MDT will be averaged across participants in recruitment blocks of thirty. Monetary costs will be assigned to all resources used to ascertain a cost for each participant, and group means and variation calculated and compared. Unit costs of resources will be based on data from local financial managers, validated national sources [63], and market prices, as appropriate, and multiplied by the number of units used.

The use of health and social care services (GP, community, outpatient, A&E, hospital inpatient) will be collected by self report at each assessment point by recall for the previous period (three months prior to baseline). Responses will be verified as far as possible (within the resources of the trial) from local records. Unit costs of services will be obtained from local and national sources [63] and multiplied by the number of units used. Costs of service utilisation in the intervention groups (A and B) will be compared with each other and with the usual care group (C) to assess the extent to which the interventions may be offset by savings elsewhere in the health and social care system.

The economic analysis will evaluate the costs of the intervention in relation to all patient and carer consequences/outcomes [64]. In addition, a cost-effectiveness analysis will be conducted, using standard techniques of economic appraisal [65]. Mean differences between groups (Group A (specialist rehabilitation only) vs. group C (normal care controls); Group B (rehabilitation with ongoing support) vs. Group A) in the primary outcome measures (disability score for patients, carer strain) and in QALYs (patients only) adjusted for baseline values in an analysis of covariance, will be used to measure effectiveness. If statistically significant differences between groups are found, incremental cost-effectiveness ratios will be calculated to show the extra cost incurred per unit of therapeutic gain/QALY gain. Secondary cost-effectiveness analyses will be conducted using other outcomes as measures of effectiveness.

The impact of uncertainties in the estimation of costs and outcome variables will be explored using one way and probabilistic sensitivity analysis. Bootstrap methods will be used to represent uncertainty of estimates, either for constructing confidence intervals or probability curves. Sensitivity analysis will also investigate the cost-effectiveness of the interventions for people with different levels of disability at baseline.

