### Interventions

#### Specialist rehabilitation intervention (Groups A and B)

A multidisciplinary team comprising two each of PNS, physiotherapist, occupational therapist, and speech and language therapist will be assembled from local professionals. They will work one day per week for the trial, and in other duties for the rest of the time. Team members will visit the homes of participants to deliver a specialist rehabilitation package, tailored to individual needs. In order to make the outcome from the trial comparable to that of the previous study set in a day hospital [10-12], a similar programme of specialist rehabilitation will be provided comprising an initial assessment, and the formation of an agreed care plan reflecting the needs, wishes and expectations of the person with Parkinson's and carers. A group education component in the day hospital trial cannot be replicated in the domiciliary setting. As a substitute, the MDT will provide participants with a folder containing 13 fact sheets produced by Parkinson's UK and the research team, covering various aspects of living with Parkinson's including: medications, physiotherapy exercises, foot care, diet and nutrition, speech and language, relaxation techniques, sleep and fatigue, continence and bowel care, rights and benefits and advice for carers.

The rehabilitation intervention will be coordinated by the PNS, and will involve specialist input from each professional, over a period of six weeks. The team will meet face-to-face four times in each six week cycle to discuss patient plans and progress, and communicate by email and telephone at other times. Two hospital consultants (neurologist and geriatrician), both with a special interest in movement disorders, can be called upon by the MDT for medication changes or advice. Referrals to a range of other professionals will be made as required, including community psychologist, social care manager, continence adviser, dietician and pharmacist. Overall three days of professional time (including travel and meeting time) is allowed for each person with Parkinson's in the trial, but some people may need more and others less than this. This input is largely equivalent to the 9-12 hours of individualised nursing and therapy input, and flexible access to other professionals, in the previous day hospital trial.

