### Outcome measures

Participants in all groups will be assessed in their homes by a research nurse, according to the schedule used in the day hospital trial, at weeks 6 (after the rehabilitation intervention), 24 (four months after the end rehabilitation, coinciding with the end ongoing support for Group B), and 36 (for final follow up). Validated instruments which reflect the needs of participants (e.g. functional outcomes, quality of life) and service commissioners (e.g. service use), and which have been found sensitive in previous rehabilitation studies undertaken by the research team [10-13] have been selected to measure outcomes (Table 1).

**Table 1 T1:** Trial outcome measures and instruments: baseline, 6, 24 and 36 weeks

Participant	Outcome measure	Instrument
Person with Parkinson's	Parkinson's disability/general activities	Self Assessment Parkinson's Disease Disability Scale [46] (PRIMARY OUTCOME)
	
	Parkinson's specific	Parkinson's Disease Questionnaire [47]
		
		Non Motor Symptom Questionnaire [48]
	
	Mobility	Posture and gait items from the Unified Parkinson's Disease Rating Scale [49]
		
		Timed up and go [50]
	
	Falls	Self report
	
	Speech	Single speech item from the Unified Parkinson's Disease Rating Scale [49]
		
		Abridged Emerson and Enderby Screening Assessment Rating Scale [51]
		
		Frenchay Dysarthria Summary [52]
		
		Speech self report questionnaire [10-12]
	
	Pain	Visual analogue scale [53]
	
	Generic health related quality of life/QALYs	Euro Qol 5D, with utility index for calculation of quality adjusted life years (QALYs) [54]
	
	Self efficacy	Self efficacy scale [55]
	
	Health and social care utilisation	Customised proforma and patient records

Live-in carer	Carer strain	Modified caregiver strain index [56] (PRIMARY OUTCOME)
	
	General health	General health questionnaire - 12 [57]

Both	Activities of daily living	Barthel ADL index [58]
	
	Social activities	Frenchay Activities index [59]
	
	Psychological wellbeing	Hospital Anxiety and Depression Scale [60]
		
		Yale single item depression screening tool [61]
	
	Generic health related quality of life	Short form - 36 Health Survey [62]

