The instrument battery was developed and piloted in collaboration with patient and carer representatives. It takes about one hour to complete, and was not been found too onerous. Research nurses will assist patients with completion of questionnaires. Carers will be asked to self complete the questionnaires that apply to them. All questionnaires will be checked for completeness before the research nurse leaves the participant's home. Data will be entered by the research nurse shortly after collection, and any queries referred back to the participant by telephone. A further check on data (completeness and entry) will be undertaken by the research manager when forms are returned to the office by the research nurse, and missing items or other issues will be resolved. Patient and carer outcomes will be analysed separately.

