### Blinding

The research administrator will not disclose group allocation to the research nurses who undertake assessments, and participants will be asked not to discuss aspects of the trial and treatments with them. However, it is recognised that blinding of the research nurses may be compromised in trials of this nature. As a check on blinding, research nurses will be asked to guess participants' groups at the end of the trial. For data analysis, the group identifiers will not be disclosed to the statistician.

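### The service-use form, as the blinded research nurse is to handle it, can disclose allocation at weeks 6 and 24, and a single guess at the end of the trial cannot show when blinding failed

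*Protocol article*

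**What the plan says.** Four parts of the protocol article bear on this.

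- **What is collected and when.** Economic evaluation: "The use of health and social care services (GP, community, outpatient, A&E, hospital inpatient) will be collected by self report at each assessment point". Patients answer from memory over the period since the last assessment. Table 1 gives the instrument as "Customised proforma and patient records", at baseline and weeks 6, 24 and 36.
- **Who collects it.** Outcome measures: "Participants in all groups will be assessed in their homes by a research nurse". The nurse helps patients fill in the questionnaires and checks them before leaving the home. Then: "Data will be entered by the research nurse shortly after collection".
- **What that nurse may know.** Blinding: "The research administrator will not disclose group allocation to the research nurses who undertake assessments". Participants are also asked to keep the trial and their treatment out of conversation with the nurses. The section accepts that blinding may fail in this kind of trial and plans one check, a guess of group by the nurses when the trial ends.
- **What there is to disclose.** Specialist rehabilitation intervention (Groups A and B): "Team members will visit the homes of participants to deliver a specialist rehabilitation package, tailored to individual needs". Group B then has care-assistant support, by home visit and telephone, until week 24.

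The article nowhere gives the service-use form to anyone other than the research nurse, and nowhere says that trial-team contacts are left off it.

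**The concern.** A patient in Group A or B who answers a question on recent community services fully may name the contacts that the Blinding section asks them not to mention. The disclosure would come from the trial's own data collection, not from a slip in conversation. It could occur at week 6, the first follow-up visit and the time of the planned short-term tests of disability and mobility.

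At stake is assessor bias in the measures that depend on the nurse's judgement or conduct of a test. The acceptability interview with Groups A and B at the week 24 assessment is a separate possible route (the article does not say who conducts it). Moving that interview would not close this one.

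**Working it through.** No stated figure is in dispute, so the check sets the sections side by side.

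**1. Recall periods against intervention periods.** Each form covers the interval since the previous assessment.

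| Visit | Recall period | Trial contacts in that period |
|---|---|---|
| Week 6 | weeks 0 to 6 | A and B: nurse specialist, physiotherapist, occupational therapist, speech and language therapist at home. C: none |
| Week 24 | weeks 6 to 24 | B: care assistant, about one hour a week, 24 − 6 = 18 weeks, so about 18 hours. A and C: no care-assistant support |
| Week 36 | weeks 24 to 36 | None; Statistical methods says all interventions have stopped by week 24 |

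A full answer can therefore separate A and B from C at week 6, and B from the other two groups at week 24. At week 36 the form adds nothing new. What remains is what a nurse remembers from an earlier visit, and the article does not say whether the same nurse returns.

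**2. How informative a reported contact is.** Background says that many patients currently see no individual therapists, and that coordinated team care is rarer still. Exclusion criteria removes anyone with a multidisciplinary package in the past six months. Individual therapy is not excluded, so one physiotherapy visit proves nothing. Four disciplines at home within six weeks, or regular care-assistant contact, is a much stronger signal.

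**3. Number of patients who could be affected.** At week 6: 2 × 90 = 180 of 270. At week 24, through care-assistant contacts: 90. These are ceilings. The share who would report trial contacts is not given and could lie anywhere from 0 to 100%.

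**4. Outcomes exposed.** The article does not say item by item who rates what, but the research nurse is the only assessor named. Most exposed are timed up and go, the posture and gait items, and the rated speech measures. The patient's primary outcome is a self-assessment scale on which the nurse only assists, so it is less exposed. Carers complete the strain index themselves.

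**5. What the planned check can show.** One guess at the end of the trial pools everything learned at weeks 6, 24 and 36, including anything learned through the week 24 interview. It cannot tell whether the week 6 or week 24 ratings were made blind.

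**The case against.** **The form is not shown.** An article may leave item wording to the full protocol, and the form may already exclude trial contacts. This stands in part: the wording is unknown, so disclosure is a risk and not a certainty. But the article does fix who handles the form, at which visits and that community services are covered, and these conflict with its own blinding instruction.

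**Usual-care patients may see therapists too, and the team is drawn from local professionals.** A single reported contact would not identify an arm. This stands, and rules out saying that the form reveals the group of every patient in A and B.

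**The primary outcomes are self-reported, and the limits of blinding are admitted.** Both are true. The first places the risk mainly in the secondary, nurse-rated measures. The second is a general caution and does not address an avoidable route.

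**A reader might infer that intervention contacts are counted twice in the costs.** The documents do not support that. Intervention resources come from the team's and care assistants' own records. The service-use comparison looks for savings elsewhere in the system, and hypothesis 1c concerns other services. Separation is intended, although no explicit rule is given. If a share f of trial contacts were also reported as community use, they would count 1 + f times, from 1.0 (f = 0) to 2.0 (f = 1). Nothing in the article fixes f, so no amount or bias can be claimed.

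**Conclusion.** The point holds as a conflict between the data-collection procedure and the blinding procedure. The nurse who must not learn the group assists with, checks and enters a form on which that group can show. The risk arises directly at weeks 6 and 24 and only by carried-over knowledge at week 36, so it would be wrong to say that the form opens this route afresh at all three visits. It concerns chiefly the nurse-rated mobility and speech outcomes. At most 180 patients could be affected at week 6 and 90 through care-assistant contacts at week 24. The size of any resulting bias cannot be derived from the article.

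This rests on two assumptions: that the form does not already exclude trial contacts, and that the research nurse makes the ratings. It is a cheap improvement worth making before follow-up visits, because ratings made with knowledge of the group cannot be repaired later. Double counting calls for a clarifying sentence only.

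**What to change.** 1. Complete the disability scale and all nurse-rated measures before any service-use question. This protects the current visit but not the next one, so step 2 is also needed.
2. Have the service-use form returned sealed to the project administrator, or taken by telephone by that person, who already knows the allocations (Registration and randomisation). The nurse then neither checks nor enters it.
3. Word the form to leave out contacts with the trial team and care assistants, which are costed from their own records. Attended referrals to other services should still count, once, as service use. Deleting every service that appears in both sources would remove genuine use, since the team's records log referrals made and not attendance.
4. Record the nurse's guess of group, with the reason, after each of the visits at weeks 6, 24 and 36.

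The cost is a change to one form, a fixed visit order, a short added item per visit and some data entry moved to the office. Without the nurse's check in the home, a few more forms will come back incomplete and need a telephone query, which the Outcome measures section already provides for. An administrator who knows the group could influence answers given by telephone, so a fixed script is advisable.

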### Statistical methods

Data will be entered into an SPSS (latest version) computer data-base using the registration number to identify the participant. All paper data will be stored in a secure locked cabinet, and all computer data will be stored on a secure server.

Baseline data will be analysed to describe the characteristics of the participants and to check for significant imbalance between the three groups. All outcomes will be analysed at each follow up assessment point (six, 24 and 36 weeks), and specific *a priori *hypotheses will be tested reflecting the outcomes that we expect to identify at the different stages. In each case a two sided test will be used. It is expected that t tests will be conducted to compare groups, unless any obvious deviations from t test assumptions are found in the outcomes, in which case the non - parametric Mann Whitney U test will be used.

In order to identify short term benefits, participants in the specialist rehabilitation groups (A and B) will be compared with participants receiving information pack only (group C) at six weeks. The null hypotheses will be tested, that there are no differences between the groups, with respect to change in patient disability, mobility and psychological wellbeing, and in carer strain. These hypotheses will be tested using each participant's change score from baseline (week 0) to week 6.

In order to identify medium term benefits, comparisons will be made at 24 weeks between pairs of treatment groups (Group A vs. Group B; Group A vs. Group C; Group B vs. Group C). The null hypotheses will be tested, that there are no differences between the groups with respect to change in patient disability, mobility, falls, speech, activities of daily living, social activities, psychological wellbeing, health related quality of life and use of health and social care services, and in carer strain, social activities and health related quality of life. These hypotheses will be tested using each participant's change score from baseline (week 0) to week 24.

In order to show loss or maintenance of benefit resulting from specialist rehabilitation, Group A (no ongoing support weeks 7 and 24) will be compared with Group B (ongoing support weeks 7 to 24) using the hypotheses in the medium term analysis and each participant's change score from week 6 to week 24.

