In order to identify longer term benefits, comparisons will be made at 36 weeks between pairs of treatment groups (Group A vs. Group B; Group A vs. Group C; Group B vs. Group C). The null hypotheses will be tested, that there are no differences between the groups with respect to change in patient disability, mobility, falls, speech, activities of daily living, social activities, psychological wellbeing, health related quality of life and use of health and social care services, and in carer strain, social activities and health related quality of life. These hypotheses will be tested using each participant's change score from baseline (week 0) to week 36.

An additional exploratory analysis will be performed using each participants change score for the above outcomes between week 24 and week 36. This is the follow-up period, and this analysis will provide evidence of trends in each group, and difference between groups, after all interventions cease in week 24.

It is recognised that multiple statistical tests are being undertaken, but no adjustments will be needed for multiple testing because *a priori *hypotheses have been stipulated, and the selective reporting of significant results will be avoided. Any additional exploratory (hypothesis generating) data analyses will make allowance for multiple testing in the usual way (Bonferroni).

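### Health and social care use is recalled over windows of about 13, 6, 18 and 12 weeks but tested by change scores, so no stated hypothesis test measures total use over the trial

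*Protocol article*

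**What the plan says.** The Economic evaluation section of the protocol article states that use of services "will be collected by self report at each assessment point by recall for the previous period (three months prior to baseline". The Outcome measures section places the assessments "at weeks 6 (after the rehabilitation intervention), 24 (four months after the end rehabilitation" and "and 36 (for final follow up".

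The Statistical methods section puts service use in the list of null hypotheses on change at 24 weeks ("health related quality of life and use of health and social care services, and in carer strain, social activities") and repeats the list at 36 weeks. It then fixes the test variable: "These hypotheses will be tested using each participant's change score from baseline (week 0) to week 24", and later "These hypotheses will be tested using each participant's change score from baseline (week 0) to week 36". Two further analyses use the same outcome list. Group A is compared with Group B on the change from week 6 to week 24, and an exploratory analysis uses the change from week 24 to week 36. Nothing in the section converts service use to a rate or adds the periods together.

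Hypothesis 1c, in the Background, is that the rehabilitation package reduces use of other services, including hospital and long-term care admissions.

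**The concern.** A change score suits an instrument that describes the patient's state on the day, such as disability or strain. Service use is different: each record is an amount accumulated over the time since the last visit. The value recorded at week 36 is therefore use during weeks 24–36, not use since randomisation.

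Two things are at stake. First, hypothesis 1c concerns how much service use the intervention saves, which is a cumulative quantity, and the named tests each look at only the last window. Second, where both windows lie after randomisation and differ in length, a change in counts can mislead about whether a benefit grew, held or faded. That is the question the week 6-to-24 and week 24-to-36 analyses are meant to answer.

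**Working it through.** The protocol gives no computed figure for service use, so there is none to reproduce.

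**Step 1: windows.** From the nominal visit weeks 0, 6, 24 and 36, the recalls cover 6 − 0 = 6, 24 − 6 = 18 and 36 − 24 = 12 weeks. Baseline covers three months, about 13 weeks.

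**Step 2: what the baseline contrasts estimate.** Randomisation makes expected baseline use equal in the arms, so it cancels from the difference in mean change. With weekly rates r1, r2 and r3 in weeks 0–6, 6–24 and 24–36, and Δ the difference between arms:

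- change 0 to 24: 18·Δr2, covering 18/24 = 75% of the time since baseline;
- change 0 to 36: 12·Δr3, covering 12/36 = 33%;
- total over 0–36: 6·Δr1 + 18·Δr2 + 12·Δr3.

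**Step 3: the later changes.** If taken on counts:

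- change 6 to 24: 18·Δr2 − 6·Δr1;
- change 24 to 36: 12·Δr3 − 18·Δr2.

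Neither is zero when the difference in rate is constant.

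**Step 4: illustrations.** I assume 1 contact per week in the comparator. Entries are differences in contacts, treated minus comparator.

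| Assumed treated rate | Total 0–36 | 0 to 24 | 0 to 36 | 6 to 24 | 24 to 36 |
|---|---|---|---|---|---|
| 20% lower, weeks 0–24 only | −4.8 | −3.6 | 0 | −2.4 | +3.6 |
| 30% higher, weeks 0–6 only | +1.8 | 0 | 0 | −1.8 | 0 |
| 20% lower throughout | −7.2 | −3.6 | −2.4 | −2.4 | +1.2 |

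For the last row, treated counts are 0.8 × 6 = 4.8, 0.8 × 18 = 14.4 and 0.8 × 12 = 9.6, against 6, 18 and 12. The change 6 to 24 is (14.4 − 4.8) − (18 − 6) = −2.4, and the change 24 to 36 is (9.6 − 14.4) − (12 − 18) = +1.2. On the weekly scale the difference is −0.2 in every period, so nothing has changed. The second row matters because the team may refer patients to other services during the first six weeks; extra use confined to that period is invisible in both baseline change scores.

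**Step 5: change within an arm at a constant rate.** Window length alone gives 18/13 − 1 = +38% (0 to 24), 12/13 − 1 = −8% (0 to 36), 18/6 − 1 = +200% (6 to 24) and 12/18 − 1 = −33% (24 to 36). If three months is read as 12 weeks, the first two become +50% and 0%. The −33% matters most, because the exploratory analysis is also meant to show trends within each group.

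**Step 6: precision.** Suppose each person has a stable weekly rate with mean m and between-person variance v, and Poisson counts.

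- Week 24: follow-up variance is 18m + 324v and change variance is 31m + 25v. Subtraction lowers the variance once v > 13m/299 = 0.043m.
- Week 36: 12m + 144v against 25m + v. Subtraction lowers the variance once v > 13m/143 = 0.091m.

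The direction depends on v, which the protocol does not give.

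**The case against.** The strongest reply is that windows are identical in all arms, so the baseline-to-24 and baseline-to-36 contrasts are valid comparisons of use in weeks 6–24 and 24–36, in size as well as sign. That stands. Use after support has stopped is also a reasonable target for a test of longer-term benefit. But neither contrast is total use, and no other stated hypothesis test supplies it.

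The section also says that all outcomes are analysed at each follow-up, and the three recalls are contiguous. So it would be wrong to infer that earlier periods are uncollected or never examined: the week-24 and week-36 tests together cover 18 + 12 = 30 of 36 weeks. Even so, the named week-6 hypotheses leave out service use, and separate looks at successive periods are not a test of the total.

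The Economic evaluation separately compares service costs between groups, not as a change score, and gives no period. It may already use totals, so the point is made against the hypothesis tests and not against the cost analysis.

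The article does not say that raw counts are subtracted, and an analysis plan that is not shown might use weekly rates. Rates would remove the distortions in steps 3 and 5. They would not make the baseline changes cover the missing weeks.

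Finally, Groups A and B receive the same package in weeks 0–6, so by design Δr1 should be near zero, and the 6-to-24 change then equals the difference in use over weeks 6–24. Its distortion needs a difference already present in weeks 0–6, for example by chance: a persistent imbalance of d contacts per week enters as (18 − 6)d = 12d instead of cancelling. The 24-to-36 change has no such protection, because a difference before week 24 is what the trial hopes to find.

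**Conclusion.** The point holds for service use only; the two primary outcomes are unaffected. The stated tests do not measure total use over weeks 0–24 or 0–36. The week-36 test uses 12 of 36 weeks and cannot see savings made during weeks 0–24: in the illustration, 4.8 contacts saved appear as none. If counts are used, a constant 20% reduction looks like a growing benefit from week 6 to 24 (−2.4) and a loss from week 24 to 36 (+1.2). These figures assume nominal visit weeks and 1 contact per week in the comparator, and scale in proportion to that rate.

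Three stronger readings are not supported:

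- A reader might infer that unequal windows bias the baseline-to-24 and baseline-to-36 contrasts. They do not, because the windows are common to all arms.
- A reader might infer that subtracting baseline adds noise, by 31/18 = 1.72 at week 24 and 25/12 = 2.08 at week 36. Those ratios need Poisson counts with no variation between people. With modest variation the effect reverses (step 6), so no general penalty is claimed.
- A reader might extend the point to falls. The article says only that falls are self-reported and gives no recall period, so the extension cannot be made.

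**What to change.** For service use, replace the change scores with between-group comparisons of total use over weeks 0–24 (6 + 18) and weeks 0–36 (6 + 18 + 12), adjusted for pre-baseline use. A count model with an offset for observed time would serve, as would a mean difference with a bootstrap confidence interval. Express any period-to-period comparison, including week 6 to 24 and week 24 to 36, as a rate per week. State in the Economic evaluation that the service cost comparison covers the same total periods.

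The cost is a change of wording in the Statistical methods and Economic evaluation sections or in the analysis plan. Every period from baseline to week 36 is already collected, so no new data, visits or participants are needed.
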